#### Patient and illness characteristics

In order to examine which patients are most likely to benefit from the intervention, we will assess various potential effect modifiers. The choice of these factors was based in part on the Dutch multidisciplinary guideline for MUPS and somatoform disorders which advocates the use of three patient profiles: mild, moderate and severe symptom profile [36]. Severity depends on factors such as duration, severity and number of symptoms and comorbidity. The potential effect modifiers selected in this study are:Demographic factors: age, gender and education (self-report)Illness duration (self-report)Severity of somatization (somatization scale of the PHQ-15 [27])Physical comorbidity (self-report)Psychiatric comorbidity: anxiety and depression (HADS [43])

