*Budget impact analysis (BIA):* in the BIA, the cost-effectiveness of the short-term psychological intervention and usual care will be extrapolated using a simple Markov model over a period of 5 years based on the estimates obtained from the proposed study. Societal, government and insurer perspectives will be considered. Different scenarios will be evaluated including the following: (1) the intervention is not implemented, i.e. all patients receive usual care, (2) the intervention is offered to the whole patient population, (3) the intervention is implemented over a period of 4 years (25% of the patient population per year) and (4) the intervention is only offered to specific subgroups of the potential patient population. These subgroups will be defined based on the results of the study (e.g. subgroups that particularly benefitted from the intervention).

The total number of patients eligible for the intervention will be estimated based on Dutch incidence and prevalence rates of USD. Resource utilisation will be calculated by multiplying the number of eligible patients with the resource utilisation rates obtained from the cost-effectiveness analysis. Different prices will be used to value resource use depending on the perspective of the analysis: Dutch standard costs for the societal perspective, actual Dutch Healthcare Authority (NZA) tariffs for the government perspective, and average NZA tariffs for the insurer perspective. Both resource use and annual costs will be presented over a 5-year period for all perspectives. Aggregated and disaggregated (e.g. GP care, secondary care, and productivity losses) total costs per year will be presented for the different perspectives and scenarios.

*Analysis of patients most likely to benefit from the intervention*: if power allows, interaction terms between potential effect modifiers (e.g. severity, comorbidity, gender) and group allocation will be tested in mixed regression models. In case of insufficient power, only exploratory analyses will be done.

*Mediation analyses*: mediation analyses will be conducted to determine whether the intervention affected physical functioning through changes in problem-solving skills, health anxiety, illness perceptions, coping, mastery and/or working alliance. The Krull and MacKinnon method [57] will be used for this purpose.

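### Budget-impact scenario 4 chooses its subgroups from the same trial results that feed the 5-year projection, so any subgroup-specific inputs are expected to be too favourable per treated patient

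*Protocol article*

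**What the plan says.** All references are to the protocol article.

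- **Choice of subgroups.** The budget impact paragraph under Economic evaluation lists four scenarios. The fourth restricts the offer to particular subgroups, and the rule for choosing them is: "These subgroups will be defined based on the results of the study (e.g. subgroups that particularly benefitted from the intervention".
- **Source of the projection.** The same paragraph says that cost-effectiveness will be "extrapolated using a simple Markov model over a period of 5 years based on the estimates obtained from the proposed study". Resource use comes from "multiplying the number of eligible patients with the resource utilisation rates obtained from the cost-effectiveness analysis".
- **Where subgroups would come from.** A later paragraph of that section says: "if power allows, interaction terms between potential effect modifiers (e.g. severity, comorbidity, gender) and group allocation will be tested". It adds: "In case of insufficient power, only exploratory analyses will be done".
- **Candidates.** Patient and illness characteristics lists five items, which make eight variables once split: age, gender, education, illness duration, PHQ-15 severity, physical comorbidity, anxiety and depression.
- **Link to costs.** The Discussion states the assumption that better functioning and quality of life will lower health care and work-related costs.

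No selection threshold, shrinkage or caveat is attached to scenario 4.

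**The concern.** An estimate picked because it is large overstates the truth on average. Here one dataset would both point to the favourable subgroup and supply the figures projected for it over five years. Scenarios 2 and 3 cover the whole patient population and involve no such selection. A payer who compares targeted with general implementation would therefore set an optimistic per-patient figure beside an unselected one.

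The risk is greater because the trial is sized for one overall comparison and has little information on differences between subgroups. An apparent best subgroup will often reflect chance.

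**Working it through.** **Inputs** (Power calculation/sample size calculation): difference 4 PCS points, SD 10, two-sided 5%, power 80%, two follow-up measurements with correlation 0.5, average cluster size 4, ICC 0.05, dropout 20%.

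**1. Reproduce the stated sample size.**
- Single measurement: 2 × (10 × (1.96 + 0.8416) / 4)² = 98.1 per arm.
- Mean of two measurements: 98.1 × (1 + 0.5)/2 = 73.6, so 74.
- Design effect: 1 + (4 − 1) × 0.05 = 1.15; 74 × 1.15 = 85.1, so 85.
- Dropout: 85 / 0.8 = 106.25, stated as 106.

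The plan's figures are reproduced.

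**2. Precision for a subgroup difference.**
- SE of the overall effect: 10 × √(2 × 0.75 × 1.15 / 85) = 1.42 points.
- SE within one half of the sample: 1.42 × √2 = 2.01 points.
- SE of the difference between two halves (the interaction): 2 × 1.42 = 2.85 points.
- Power for a 4-point interaction: Φ(4/2.85 − 1.96) = Φ(−0.56), about 29%.
- Interaction needed for 80% power: 2.80 × 2.85, about 8 points, or twice the target effect.

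**3. Expected effect in the better-looking half when nobody differs.** Assume (not in the article) independent modifiers, each splitting the sample 50/50, and a true effect of 4 points in everyone. The two halves of a modifier show the overall estimate plus and minus half its interaction estimate. The expected best half over K modifiers is therefore 4 + 1.42 × E(max of K values of |Z|), with Z standard normal.

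| K | E(max of absolute Z) | Best half, points | Excess |
|---|---|---|---|
| 1 | 0.80 | 5.1 | 1.1 (28%) |
| 5 | 1.57 | 6.2 | 2.2 (56%) |
| 8 | 1.78 | 6.5 | 2.5 (64%) |

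A simulation of individual patients with randomly varying split sizes gave 6.3 (K = 5) and 6.6 (K = 8). It gave about the same excess when the true effect was 2 or 0.

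**4. Selecting only after a significant interaction.** The chance of at least one false positive is 1 − 0.95⁵ = 23% or 1 − 0.95⁸ = 34%. In those trials the chosen half shows about 7.4 points on average. A significance gate makes selection rarer but the selected estimate larger.

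**5. Does this make scenario 4 beat full roll-out?** Count benefit per eligible patient and take savings as proportional to PCS gain. Half the patients at 6.5 points give 0.5 × 6.5 = 3.25, against 4.0 for treating everyone. So full roll-out still shows the larger gross gain. Let c be the delivery cost per treated patient, expressed in points' worth of savings. Scenario 4 comes out ahead if 0.5 × (6.5 − c) > 4 − c, that is c > 1.5. With the true effect it would need 0.5 × (4 − c) > 4 − c, that is c > 4. Selection thus lowers the bar for targeting, but neither c nor the saving per point is in the article.

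**The case against.** **Subgroup-specific inputs are not stated.** The article gives benefit only as an example of how subgroups may be defined, and does not say whether the resource-use rates are whole-trial or subgroup-specific. If whole-trial rates and effects were used, this inflation would not arise. That stands, and the conclusion is conditional on it. A scenario built around those who benefitted most would, however, have little purpose with whole-trial inputs.

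**There are safeguards.** The candidate modifiers are listed beforehand, and underpowered analyses are called exploratory. Both help in part. The list shortens the search, but the choice within it still follows the results. The exploratory label applies to the modifier analysis, and nothing keeps an exploratory subgroup out of scenario 4.

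**The illustration is near the upper end, and in the wrong unit.** It takes the best half over several independent even splits; real splits may be uneven. Strong true effect modification would make the relative excess smaller. Budget impact is reported in resource use and euros, not PCS points. All of this stands. The sign of the bias does not depend on these choices, and one modifier already adds about 1.1 points.

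**A condensed article leaves detail elsewhere.** Shrinkage and thresholds may well be set out in a fuller plan. The point here concerns the selection rule that the article does state.

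**Stronger readings.** A reader might infer that scenario 4 will look better than full roll-out even if every patient benefits equally. Step 5 shows that this does not follow. A reader might also infer a known overstatement of savings. No cost figure can be derived, and the only bridge from PCS to costs is the assumption in the Discussion.

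**Conclusion.** The point holds in conditional form. The stated rule lets the same data choose the scenario 4 subgroups and project them. If subgroup-specific inputs are used uncorrected, the effect per treated patient is expected to be too favourable, and so are savings to the extent that costs follow benefit. The per-patient comparison with scenarios 2 and 3 is then tilted toward targeting.

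Under the stated assumptions the excess is roughly 1.1 points for a single modifier and 2.2 to 2.5 for five to eight, on a true effect of 4. These figures show the order of size and do not predict this trial's result. The euro amount and the ranking of scenarios on total budget remain undetermined.

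Severity is minor: one of four scenarios in a secondary model is affected. This is a cheap improvement.

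**What to change.** Adopt one of two routes and state it in the analysis plan.

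1. **Define the scenario 4 subgroups before outcome data are analysed**, from variables already collected under Patient and illness characteristics. The article notes that the guideline "advocates the use of three patient profiles: mild, moderate and severe symptom profile", but gives no cut-offs, so the study team would have to write down its own definitions. This removes the selection. Subgroup estimates stay imprecise (SE about 2.0 points for half the sample), so their uncertainty should be carried into the model.
2. **If the subgroups are chosen from the data**, feed the model either the overall effect or shrunken or bootstrap optimism-corrected subgroup effects and costs, with their uncertainty. The subgroup selection must be repeated within each bootstrap sample. Label scenario 4 exploratory.

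Under either route, say whether effects and resource-use rates in scenario 4 are whole-trial or subgroup-specific. Excluding data-found subgroups from the budget model altogether would be a preference and is not required.

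The cost is a few sentences and a little more analysis, with no new data. The downside is that scenario 4 will probably look less favourable.

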### Care as usual (CAU) group

Patients in the CAU group will not be offered any additional specific intervention other than the care that they would usually receive from the GP and/or MHNP, carried out according to the guideline for medically unexplained symptoms by the Dutch College of General Practitioners (NHG) [36].

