### Outcome measures

An overview of all outcome measures and the time points of assessments can be found in Table 2.

**Table 2 Tab2:** Overview of assessment moments and outcome measurements

	Instrument	Baseline (T0)	2 months (T1)	4 months (T2)	8 months (T3)	12 months (T4)
Primary outcomes						
Physical functioning	PCS of RAND-36	x	x	x		x
Direct and indirect costs	Tic-P	x		x	x	x
Quality of life	EQ-5D-5L	x	x	x	x	x
Secondary outcomes						
HRQoL	RAND-36 subscales	x	x	x		x
Anxiety and depression	HADS	x	x	x		x
Number/severity of symptoms	PHQ-15	x	x	x		x
Potential mediators						
Health anxiety	Whitely Index	x	x	x		
Illness perceptions	Brief IPQ	x	x	x		
Cognitions and coping	CBRQ	x	x	x		
Social problem-solving skills	SPSI-R:S	x	x	x		
Mastery	Pearlin Mastery Scale	x	x	x		
Working alliance	WAI-SF^a^		x	x		

*PCS* physical component summary score, *RAND-36* RAND-36-item Health Survey, *Tic-P* Trimbos and iMTA questionnaire on Costs associated with Psychiatric Illness, *EQ-5D-5L* EuroQol 5D – 5 level version, *HRQoL* health-related quality of life, *HADS* Hospital Anxiety and Depression Scale*, PHQ-15* Patient Health Questionnaire somatization scale, *IPQ* Illness Perception Questionnaire, *CBRQ* Cognitive and Behavioural Responses Questionnaire, *SPSI-R:S* Social Problem-solving Inventory Revised: Short Form, *WAI-SF* Working Alliance Inventory-Short Form

^a^only administered in the intervention group

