#### Potential mediators

The intervention is expected to have positive effects on physical functioning and quality of life through developing problem-solving skills and increasing adequate coping. Moreover, health anxiety and dysfunctional somatic causal attributions are thought to be important aggravating factors of somatoform disorders which are reflected in the new DSM-5 criteria for somatic symptom disorder (formerly somatoform disorders) [44]. Therefore, the following factors will be assessed as potential mediators:Problem-solving skills (Social Problem-solving Inventory [45])Health anxiety (Whiteley Index [46])Illness perceptions (brief IPQ [47])Coping and beliefs about symptoms (CBRQ [48])Mastery (Pearlin Mastery Scale [49])Working alliance (WAI-SF [50])

The Social Problem-solving Inventory Revised: Short Form (SPSI-R:S) measures an individual’s problem-solving strengths and weaknesses. It assesses five dimensions: positive problem orientation, rational problem solving, negative problem orientation, impulsive/careless style and avoidance style. It consists of 25 items that can each be scored on a 5-point Likert scale (0 = ‘not at all true for me’ to 4 = ‘extremely true for me’). Higher scores indicate greater effective social problem-solving skills [45].

The Whiteley Index is a short instrument measuring health anxiety and is often used in investigating symptoms of hypochondria. It consists of 14 items with two answer categories ‘yes’ and ‘no’. A higher score indicates greater health anxiety [46].

The brief Illness Perception Questionnaire (IPQ) is based on the widely used IPQ-R. It is designed in order to rapidly assess the cognitive and emotional representations of illness. It comprises nine items in total. Five items assess cognitive illness representations: consequences, timeline, personal control, treatment control and identity. Two items assess emotional representations: concern and emotions. One item assesses illness comprehensibility. The last item is an open-ended question assessing causal representation [47].

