The Cognitive and Behavioural Responses Questionnaire (CBRQ) measures patients’ cognitive and behavioural responses to their illness. This tool has been developed to measure specific cognitions and coping styles in patients with physical symptoms. It consists of 41 items that can be rated on a 5-point Likert scale ranging from ‘strongly disagree’ to ‘strongly agree’. These items add up to four cognitive subscales: catastrophising, damaging beliefs, embarrassment avoidance and symptom focussing; and two behavioural subscales: all-or-nothing behaviour and avoidance/resting behaviour [48].

The Pearlin Mastery Scale measures the level of perceived control, or mastery, over situations in one’s life. It comprises seven items that are scored on a 5-point Likert scale, ranging from ‘completely disagree’ to ‘completely agree’ [49].

The Working Alliance Inventory-Short Form (WAI-SF) is a shortened version of the Working Alliance Inventory (WAI). It is used to measure the therapeutic alliance in an ongoing client-therapist interaction. It comprises 12 items that are scored on a 5-point Likert scale, ranging from ‘never or rarely’ to ‘very often’ [50].

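### Working alliance is listed as a mediator of the intervention effect but is measured in the intervention arm only, so the indirect effect through it cannot be estimated

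*Protocol article*

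**What the plan says.** Under Statistical analyses, the protocol article states that "mediation analyses will be conducted to determine whether the intervention affected physical functioning". The six routes it names for such an effect end with working alliance: "through changes in problem-solving skills, health anxiety, illness perceptions, coping, mastery and/or working alliance". One technique is named for all six factors: "The Krull and MacKinnon method [57] will be used for this purpose". The section Potential mediators lists the WAI-SF with the other five instruments, the abstract names working alliance in the same role, and Table 2 places it under its mediator heading.

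Table 2 also fixes when and in whom each instrument is given. The other five mediators are scheduled at baseline (T0), 2 months (T1) and 4 months (T2), with no restriction by arm. The WAI-SF is scheduled at T1 and T2 only, and its footnote reads "only administered in the intervention group".

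Two further statements bear on the point. Of the WAI-SF the article says: "It is used to measure the therapeutic alliance in an ongoing client-therapist interaction". Of the control arm it says that patients get nothing specific "other than the care that they would usually receive from the GP and/or MHNP". A CAU patient may therefore also have a relationship with a treating professional.

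**The concern.** A claim that the intervention worked through a factor is a claim about a difference between arms: allocation must have shifted the factor, and the factor must have shifted the outcome. The article commits to that question for working alliance, yet its own assessment schedule removes the control-arm data needed for the first half. The two statements cannot both be carried out.

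At stake is one of the six named mediation questions. If the wording stays, the analyst must either drop this mediator after the fact, fill in the control arm by assumption, or report a correlation among treated patients under the name of mediation. The last would tell readers something about why the treatment works that the data cannot show.

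**Working it through.** **Arm size.** The article's own figures reproduce. For a 4-point difference, SD 10, two-sided 5% and 80% power, the single-measurement size is 98.1 per arm. With two follow-up measurements correlated 0.5, 98.1 × (1 + 0.5)/2 = 73.6, giving the stated 74. The design effect is 1 + (4 − 1) × 0.05 = 1.15, and 74 × 1.15 = 85.1 (stated 85). Allowing for 20% dropout, 85/0.8 = 106.25 (stated 106). So about 106 patients per arm, 212 in all. None of these figures is disputed; they only show how many patients have no WAI-SF.

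**The two regressions.** Let X be allocation (1 = intervention, 0 = CAU), M the WAI-SF score and Y the PCS. Leaving out random effects, which do not alter the argument:

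- Mediator model: M = i + aX + error, so a = mean(M | X = 1) − mean(M | X = 0) = m₁ − m₀.
- Outcome model: Y = j + c′X + bM + error.
- Indirect effect: a × b = (m₁ − m₀) × b.

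**What the schedule supplies.** M is observed only where X = 1.

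| Model | Columns | Rank on rows with WAI-SF | Rank if measured in both arms |
|---|---|---|---|
| Mediator on arm | intercept, X | 1 of 2 | 2 of 2 |
| Outcome on arm and mediator | intercept, X, M | 2 of 3 | 3 of 3 |

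On the observed rows X is always 1 and cannot be told apart from the intercept. Hence a is not estimable and neither is c′. The slope of Y on M is estimable, but only among intervention patients. Adding patients changes none of these ranks, so the problem is one of identification and not of power. It does not depend on the details of the named technique, since any such technique needs both arms among the patients with mediator data.

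**What a constant for CAU would do.** If CAU patients are given an assumed mean m₀, the indirect effect becomes (m₁ − m₀) × b, and each one-point change in the assumption moves it by b. As an illustration with assumed values that are not in the article (m₁ = 3.5, b = 3 PCS points per WAI-SF point):

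- m₀ = 1: (3.5 − 1) × 3 = +7.5
- m₀ = 3.5: (3.5 − 3.5) × 3 = 0
- m₀ = 4: (3.5 − 4) × 3 = −1.5

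Size and sign both follow from the chosen m₀, and the planned data cannot favour one value over another. The illustration shows dependence on the assumption; it does not measure the error.

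**The baseline.** The estimate of a needs m₁ and m₀ after randomisation. It does not need M at T0. Had the WAI-SF been given in both arms at T1 and T2 only, both models would have full rank.

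**The case against.** **It is explanatory, and the restriction is printed.** This stands as to severity. The article speaks of potential mediators, working alliance is one of six, and any reader can see the footnote. It does not resolve the contradiction.

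**The statistical analysis plan will settle it.** A plan could relabel the analysis, but it cannot supply values that the protocol says are not collected. Nor is this a detail lost in condensing: the article states both the analysis and the restriction.

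**A within-arm analysis is what is meant.** The article does not say so. It asks whether the intervention affected functioning and names one technique for all six factors.

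**CAU patients have no alliance, so zero is right.** The article allows them usual contact with the GP and/or MHNP, so zero does not hold by definition.

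Three stronger readings are tempting, and the article does not support them.

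- *The missing baseline score makes the analysis impossible.* It does not, as the working shows. The article describes the scale as measuring a relationship already under way, so a score before the first session would mean little. What remains is a mismatch with the word for change in the mediation sentence, and even then a change from T1 to T2 exists within the intervention arm.
- *Filling in zero for CAU would turn the mediator into a copy of allocation.* It would not. Scores would still vary among intervention patients and the outcome model would have full rank. The valid objection is the reliance on an untestable constant.
- *The trial will report an artefactual mediated proportion.* The article plans no mediated proportion and no filling-in of CAU alliance scores. Multiple imputation is mentioned only for missing cost and effect data in the economic evaluation.

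**Conclusion.** The contradiction is real and follows from the article's own text. The mediation analysis of working alliance cannot be carried out as written, because no CAU patient (about 106 of 212) has a value, and the indirect effect is therefore not identified at any sample size. The conclusion rests on reading the Table 2 footnote literally and on taking mediation to mean an effect of allocation carried through the factor, which is how the article phrases it.

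The scope is narrow. A reader might infer that the mediation programme as a whole, or the trial's main conclusion, is compromised. It is not: the other five mediators are scheduled in both arms at three time points, and the PCS analysis, the secondary outcomes, the sample size and the economic evaluation do not use the WAI-SF. Severity is minor to moderate.

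**What to change.** Remove working alliance from the list under Potential mediators and from the mediation sentence under Statistical analyses, and move its row in Table 2 out of the mediator group. Describe it instead as a process or predictor analysis within the intervention arm: WAI-SF at T1 and T2 against PCS measured later (T2 and T4 for the T1 score, T4 for the T2 score), allowing for clustering of patients within MHNPs and labelled associational. The choice of covariates can be left to the statistical analysis plan.

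The cost is wording only. The scheduled WAI-SF data suffice, with no extra questionnaire, visit or patient burden. Recruitment was still under way when the article was submitted, so at that stage the change could precede any analysis. Giving the scale in both arms, with respect to the treating GP or MHNP, would restore a contrast between arms but would add data collection.
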